# Participant recruitment procedures: Adolescents and their families will be recruited via the health system, the education system and from the general community. Paediatric specialists and allied health professionals will be asked to identify potentially suitable adolescents. Print and radio mass media will be used to inform the general community of the study. In addition to these sources, participants will be recruited from workplaces that employ a large number of adolescents, within the Perth metropolitan area using the snowball technique [36]. Volunteers will be screened to ensure they meet the inclusion and exclusion criteria. Inclusion criteria will be: males and females aged 12-16 years; body mass index higher than the 85^th^ percentile (includes children who are typically classified as overweight or obese; [37]). Children will be excluded if they: are obese due to identified genetic factors; have morbid obesity (BMI z score higher than 3.5); have a metabolic/endocrine disease; are unable to attend twice weekly sessions, are undergoing treatment for psychiatric disorders or are assessed as unsafe to participate. Volunteers will be approved for participation by their medical practitioner.

**Sample size:** A sample size of 96 is required at post test in the intervention group to detect a 20% difference in the outcome variables at 80% power and 5% level of significance. A small effect size (0.2) is assumed for studies on behavioural effects due to the influence of extraneous variables and the subtleties of human performance. Allowing for an attrition rate of 30%, 124 adolescents and their families will be recruited into the intervention.

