# Study design: A wait-list controlled, staggered-entry cohort design will be used. Participants will be recruited and given an initial assessment then reassessed after 3 months waiting (just before starting the program). The dual pre-participation assessments will provide a within-subjects control period. Follow-up assessments will be conducted immediately after completing the program (3 months after second pre-program assessment) and at 3, 6 and 12 months post program.

Cohorts of 12-15 overweight adolescents and their parents will be progressively recruited over the study period. Cohorts are expected to start in Perth metropolitan October 2011, February 2012 and April 2012. The staggered start will control for external seasonal and public event confounders to intervention effects.

Table 1. Project community engagement (*), implementation cohorts (shaded) and follow up assessments (x)

| **Cohort** | **2011** | | | | **2012** | | | | **2013** | | | |
| --- | --- | --- | --- | --- | --- | --- | --- | --- | --- | --- | --- | --- |
|  | 1/4 | 2/4 | 3/4 | 4/4 | 1/4 | 2/4 | 3/4 | 4/4 | 1/4 | 2/4 | 3/4 | 4/4 |
| South metro | * | * | recruit | waitlist | S1 | S2 | S3x | x | x | x | x |  |
| East metro | * | * | recruit | waitlist | N1 | N2 | N3x | x | x | x | x |  |
| Regional | * |  | * | * | recruit | waitlist | R1 | R2 | x | x | x | x |

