**Evaluation**

There is substantial agreement that interventions for overweight young people need to be evaluated in terms of process and outcome and not just immediate impact (Livingstone et al 2007) to understand not only how much the intervention works but why and for whom.

**Process evaluation:** A broad process evaluation will be conducted in line with the recent framework for mandatory evaluation to ensure well informed public policy decisions [38] and recommendations by the recent Cochrane review for obesity interventions [11]. Questionnaire surveys of participants, focus groups of participants and program facilitators are anticipated [39].

Program fidelity will be assessed through observations of sessions, review of program notes and focus groups with program staff [40]. Program dose will be assessed by attendance records. Barriers to participation will be explored through participant/parent surveys including reasons for non attendance and gaining reasons for drop out from those who do not complete the program [41]. Participant satisfaction will be assessed with a validated tool [42] along with focus groups. Monitoring will also be conducted for potential adverse effects, specifically: changes in linear height, disordered eating, and psychological well being [11].

**Impact evaluation:** Immediate impact of the intervention will be assessed by comparing the changes over the 3 months between pre program assessment and immediately post program assessment with any changes over the 3 months ‘wait-list’ period between initial assessment and pre program assessment.

The primary impact measures will be changes in: 1) leisure time spent in light and moderate/vigorous physical activity; 2) leisure time spent in sedentary activity; 3) number of weekly serves of fruit and vegetables and 4) number of weekly serves of extras.

Secondary impact measures will include: readiness to change state, exercise self efficacy and food self efficacy, meeting of sedentary screen time, vigorous physical activity and key diet target behaviours.

**Outcome evaluation:** The longer term changes in behaviour (same variables as short term impact), as well as physical and mental well being and family functioning, will be assessed by comparing changes between assessments at baseline and at 3, 6 and 12 months post intervention.

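### The 80% power stated for 96 adolescents does not follow from an effect size of 0.2 for the planned within-person comparison

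*Protocol*

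**What the plan says.** The Sample size paragraph in the Protocol's Methods says "A sample size of 96 is required at post test in the intervention group to detect a 20% difference in the outcome variables". The power it claims for this is 80%, with significance set at 5%. The paragraph's next sentence says "A small effect size (0.2) is assumed for studies on behavioural effects". It names no test, sidedness, mean, SD or within-person correlation, and it does not say whether 0.2 is in SDs of the outcome or SDs of a change.

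The design has one group. On the two assessments before the program, Study design says "The dual pre-participation assessments will provide a within-subjects control period". Under Evaluation, the immediate impact is assessed by "comparing the changes over the 3 months between pre program assessment and immediately post program assessment with any changes over the 3 months" of the wait-list period. The primary impact measures are times and counts, for example the "number of weekly serves of fruit and vegetables". Expected program outcomes then anticipates a 10% change in each of four behaviours: physical activity, sedentary behaviour, fruit and vegetable serves, and junk-food serves.

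**The concern.** The Protocol itself fixes the sample size, power, significance level and effect size, so the four can be checked against one another. An effect of 0.2 SD is small, and 96 people are few for detecting it in a one-sample or paired test. The declared contrast is also noisier than a simple pre-post change, because it subtracts one change from another.

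The effect is stated in two ways, as 20% and as 0.2, with nothing to convert one into the other. A third figure, 10%, appears as the expected change.

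At stake is how the results are read. A stated power of 80% invites a reader to take a null result on activity or diet as evidence against the assumed effect. That inference needs a power the trial may not have.

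**Working it through.** **Inputs.** From the Sample size paragraph: n = 96 at post test, power 80%, significance level 5%, effect size 0.2. From Study design and Impact evaluation: one group, with initial (Y1), pre-program (Y2) and post-program (Y3) assessments. Assumed, because the Protocol is silent: two-sided testing (one-sided also shown), equal SD at each assessment, and the within-person correlation r.

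**Step 1. Trying to reproduce 96 from 0.2.** For a paired or one-sample test with 0.2 in SDs of the tested difference, the normal approximation gives n = ((1.96 + 0.84)/0.2)² ≈ 196. The exact noncentral t calculation gives 199 two-sided and 156 one-sided. A two-group comparison of means needs about 393 per group, and the design has no second group. None of these gives 96.

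The number does arise elsewhere. Two independent proportions of 0.35 and 0.55 need 96 per group, and the precision formula gives 1.96² × 0.25/0.10² = 96.04. Neither suits a single group with time and count measures, and either origin would be a guess.

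**Step 2. Power at 96 with 0.2 in SDs of the tested difference.** The noncentrality is 0.2 × √96 = 1.96. Power is 49.2% two-sided and 61.8% one-sided. The smallest standardised effect with 80% two-sided power is 0.289.

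**Step 3. Power at 96 with 0.2 in outcome SDs.**

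- Simple change Y2 to Y3: variance 2(1 − r)SD², so the standardised effect is 0.2/√(2(1 − r)).
- Impact contrast (Y3 − Y2) − (Y2 − Y1) = Y3 − 2Y2 + Y1: under equal correlations the variance is (1 + 4 + 1 − 4r − 4r + 2r)SD² = 6(1 − r)SD², three times that of the simple change.
- Under first-order autoregression, AR(1), the contrast has variance (6 − 8r + 2r²)SD².

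| r (assumed) | Simple pre-post change | Impact contrast, equal correlations | Impact contrast, AR(1) |
|---|---|---|---|
| 0.5 | 49% | 20% | 23% |
| 0.7 | 71% | 30% | 38% |
| 0.8 | 87% | 43% | 54% |
| 0.9 | 99% | 71% | 85% |

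Power of 80% needs 0.2/√(variance factor) = 0.289. That gives r = 1 − (0.2/0.289)²/2 ≈ 0.76 for the simple change and r = 1 − (0.2/0.289)²/6 ≈ 0.92 for the impact contrast. Under AR(1) the contrast needs r of about 0.89.

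**Step 4. What 96 can detect on the impact contrast.** The detectable difference-in-change with 80% power is 0.289 × √(6(1 − r)) outcome SDs. This is 0.50 at r = 0.5, 0.39 at 0.7, 0.32 at 0.8 and 0.22 at 0.9 (equal correlations).

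**Step 5. The 20%, the 0.2 and the 10%.** If 20% is relative to a mean, the effect in SDs is 0.2 × mean/SD. This equals 0.2 only when the SD equals the mean. With an SD of half the mean it would be 0.4, and with an SD of 0.7 of the mean, 0.29. The Protocol gives neither a mean nor an SD. On any one such scale a 10% change is half of a 20% change, and since n varies as 1/effect² it needs about four times the sample.

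**The case against.** The strongest reply is that the paragraph leaves so much unstated that it cannot be shown to be false. In outcome-SD units a simple pre-post change with r of about 0.76 gives exactly the stated 80% at 96. The aims are worded as comparisons before and after participation, and the outcome evaluation compares baseline with later follow-up. Both are simple changes, and the paragraph does not say which comparison was sized. It also never says outright that 20% and 0.2 are the same quantity. Finally, the Analysis plan promises adjusted mean changes with 95% confidence intervals, so a reader would see any imprecision.

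Much of this stands, and it rules out stronger readings that a reader might infer:

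- That the true power is 49%. That figure needs a two-sided test with 0.2 in SDs of the tested difference, or a simple change in outcome SDs with r = 0.5.
- That the impact contrast always has less than an even chance of success. If 0.2 is in SDs of the contrast itself, its power is the same 49%. In outcome SDs it passes 49% once r exceeds about 0.83 (about 0.78 under AR(1)), and it is 71% at r = 0.9 under equal correlations.
- That a null result would necessarily be misread. The confidence intervals reduce that risk.

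The reply does not rescue the statement. The r of 0.76 is nowhere stated. It also serves a simple change, whereas Impact evaluation defines the effect on the primary impact measures as a difference between two changes.

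**Conclusion.** Wrong as written. Power of 80% with 96 adolescents does not follow from an effect size of 0.2 for the within-person design. With 0.2 in SDs of the tested difference, 96 is less than half of the 199 required. With 0.2 in outcome SDs, the declared impact contrast reaches 80% only at a very high within-person correlation that the Protocol does not state.

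The failure to reproduce the figure is firm. The particular power is not: it depends on sidedness, on the scale of the effect and on r, and the table assumes equal SDs at each assessment. The mismatch between 20%, 0.2 and 10% is a separate defect of the same paragraph and does not depend on r.

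**What to change.** Rewrite the Sample size paragraph for the contrast defined under Impact evaluation:

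- Remove the unconditional claim of 80% power at 0.2.
- State the test, its sidedness, the scale of the effect (outcome SD or change SD) and the assumed within-person correlation with its basis.
- Give the difference-in-change that 96 can detect with 80% power over a range of correlations, as in step 4 of the working.
- Either define the 20% with a mean and SD and reconcile it with 0.2 and the 10% expected changes, or delete it.

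Do not put 49% in place of 80% as a flat figure. That would replace one unstated assumption with another.

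The cost is Protocol wording only, and the stated performance will look less favourable. This correction needs no extra recruitment.

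### The recruitment target of 124 adds 30% to the 96 needed instead of dividing by 0.70, so at the stated attrition it leaves about 87 at post test

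*Protocol*

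**What the plan says.** The Sample size paragraph in the Protocol's Methods gives three linked figures.

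- The number needed: "A sample size of 96 is required at post test in the intervention group", to be detected "at 80% power and 5% level of significance".
- The attrition allowance and the resulting target: "Allowing for an attrition rate of 30%, 124 adolescents and their families will be recruited into the intervention".

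The Study design paragraph and its Table 1 also bear on the target. The text says "Cohorts of 12-15 overweight adolescents and their parents will be progressively recruited over the study period". The South metro row of the table reads "recruit | waitlist | S1 | S2 | S3x"; the East metro row has the same form with N1 to N3, and the Regional row shows R1 and R2. Neither the text nor the table gives a total number of cohorts.

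**The concern.** An attrition rate is a share of those recruited, so the number to recruit is the number needed divided by the proportion retained. Here the rate seems to have been applied to the completers instead. That always gives too small a target, and the gap widens as the attrition rate rises.

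This paragraph is the document's only sample-size justification. Each participant acts as their own control over the waiting period, so no separate control arm exists that could make up for lost completers. If the paragraph's assumptions come true, the trial ends with fewer post-test adolescents than it says it needs.

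**Working it through.** Inputs, all from the Sample size paragraph: 96 needed at post test, 30% attrition, 124 to be recruited, 80% power, 5% significance. Sidedness is not stated; two-sided is assumed below.

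**1. Reproduce the Protocol's figure.** Needed × (1 + rate) = 96 × 1.3 = 124.8. Dropping the decimal gives 124, the stated target (rounding up would give 125).

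**2. The figure that 30% attrition requires.** Needed / (1 − rate) = 96 / 0.70 = 137.1, so 138. Check: 138 × 0.70 = 96.6, which is enough; 137 × 0.70 = 95.9, which is not. The target is 138 − 124 = 14 families below this.

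**3. What 124 recruits leave.** 124 × 0.70 = 86.8, about 87. The shortfall is 96 − 87 = 9 adolescents, or 9/96 = 9%.

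**4. The attrition that 124 can absorb.** 1 − 96/124 = 28/124 = 22.6%.

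**5. Effect on power, taking 80% at 96 as given.** Under a normal approximation, 80% power at two-sided 5% corresponds to a standardised signal of 1.960 + 0.842 = 2.802. The signal scales with the square root of the sample size:

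- At 87: 2.802 × √(87/96) = 2.667. Then 2.667 − 1.960 = 0.707, and Φ(0.707) = 0.760.
- Power at 87 is therefore about 76%.

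**6. Secondary check, the cohort grid.** Table 1 appears to label 3 + 3 + 2 = 8 cohorts. If each label is one group of 12 to 15, the places number 8 × 12 = 96 to 8 × 15 = 120. The upper figure is 124 − 120 = 4 below the target. A full 120 at 30% attrition would leave 120 × 0.70 = 84.

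**The case against.** **The 30% might run to the last follow-up.** The Protocol also plans assessments 3, 6 and 12 months after the program. If 30% is the loss by 12 months, loss by post test could be smaller, and 124 would suffice if it were at most 22.6%. But the document attaches 96 to post test, gives one attrition rate and applies it directly to that number. The exact match with 96 × 1.3 also points to a slip of formula. If a lower post-test rate is meant, the paragraph has to say so.

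**The loss is small and the power figure is conditional.** Both points stand. The move from 80% to about 76% is modest, and it borrows the 80% from the Protocol. The paragraph does not show how 96 was derived. It states "A small effect size (0.2) is assumed for studies on behavioural effects"; read as a standardised mean change in a paired comparison, 0.2 would need (2.802/0.2)² = 196.2, so 197. Whether 96 is right is a separate question, and this point takes it as given. The Analysis plan also uses mixed models, so an adolescent without a post-test value still contributes the waiting-period change. That softens the loss but does not supply the missing post-program change.

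**A reader might infer that the scheduled cohorts cannot hold 124.** The document does not establish that. Eight is a count of cell labels. The table's caption marks implementation cohorts by shading, which is not visible in the text at hand, and one group per label is an inference. The start dates are described only as expected, and those in the text do not line up plainly with the quarters in the grid. Even on the count of eight, the gap is 4 places, or 124/8 = 15.5 per cohort against 15. A still larger shortfall, obtained by running every label at the minimum of 12, is not supported either: the Protocol plans 124 recruits and nowhere plans 96.

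**Conclusion.** The attrition allowance is wrong as written. With 96 needed and 30% lost, 124 recruits leave about 87, 9 short. The target covers attrition of at most 22.6%, and holding 96 at 30% takes 138. This follows from one paragraph by arithmetic, and nothing elsewhere in the document cures it.

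The fall in power to about 76% is an illustration. It assumes two-sided testing, a normal approximation, completers only, and that 96 does give 80%. The slip does not affect bias or type I error. It should still be corrected, because the headline recruitment number does not deliver the number the trial says it needs.

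The cohort grid supports only a request for clarification, not a finding that the target is out of reach.

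**What to change.** Correct the Sample size paragraph in one of two ways.

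- Keep 124, state that about 87 are expected at post test with 30% attrition, and correct the power statement to match. On the Protocol's own footing that is about 76%; a fresh calculation would need the derivation of 96 to be shown.
- Or state that 124 covers attrition of up to 22.6%, and that 138 would be needed to keep 96 at 30%.

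Also state how many cohorts are planned and whether each Table 1 label is one group, and reconcile the resulting places with the target.

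Restating the figures costs protocol wording and no extra participants. Actually recruiting 138 would mean 14 more families; with one group of at most 15 per cohort, that is 138/15 = 9.2, so 10 cohorts against the eight labels that appear in Table 1.

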**Evaluation**

There is substantial agreement that interventions for overweight young people need to be evaluated in terms of process and outcome and not just immediate impact (Livingstone et al 2007) to understand not only how much the intervention works but why and for whom.

**Process evaluation:** A broad process evaluation will be conducted in line with the recent framework for mandatory evaluation to ensure well informed public policy decisions [38] and recommendations by the recent Cochrane review for obesity interventions [11]. Questionnaire surveys of participants, focus groups of participants and program facilitators are anticipated [39].

Program fidelity will be assessed through observations of sessions, review of program notes and focus groups with program staff [40]. Program dose will be assessed by attendance records. Barriers to participation will be explored through participant/parent surveys including reasons for non attendance and gaining reasons for drop out from those who do not complete the program [41]. Participant satisfaction will be assessed with a validated tool [42] along with focus groups. Monitoring will also be conducted for potential adverse effects, specifically: changes in linear height, disordered eating, and psychological well being [11].

**Impact evaluation:** Immediate impact of the intervention will be assessed by comparing the changes over the 3 months between pre program assessment and immediately post program assessment with any changes over the 3 months ‘wait-list’ period between initial assessment and pre program assessment.

The primary impact measures will be changes in: 1) leisure time spent in light and moderate/vigorous physical activity; 2) leisure time spent in sedentary activity; 3) number of weekly serves of fruit and vegetables and 4) number of weekly serves of extras.

Secondary impact measures will include: readiness to change state, exercise self efficacy and food self efficacy, meeting of sedentary screen time, vigorous physical activity and key diet target behaviours.

**Outcome evaluation:** The longer term changes in behaviour (same variables as short term impact), as well as physical and mental well being and family functioning, will be assessed by comparing changes between assessments at baseline and at 3, 6 and 12 months post intervention.

Physical status: Adiposity, cardiovascular fitness, muscle strength and power and motor competence will be assessed. Mental status: Attitudes to PA, moods and feelings, self perception and quality of life will be assessed. Family functioning will also be assessed.

**Expected program outcomes:** The primary program outcomes are expected to be improved adolescent behaviours including: an increase in physical activity (10% change)**;** reduction in sedentary behaviours (10% change)**;** an increase in fruit and vegetable serves (10% change)**;** a reduction in “junk food” serves (high fat, high sugar foods) (10% change)**.** We also anticipate improved physical health status; improved mental health including anxiety, depression, self worth, perceived physical appearance, physical ability and social support**;** improved quality of life and improved family functioning. We also anticipate improved parental mental health.

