# Enhancing activity, nutrition and mental health in overweight adolescents: Stage 2 Ethics Research Plan

**Aims/objectives of the study**

This study will use a wait-list controlled, staggered entry trial to assess the impact of a multidisciplinary intervention by:

1) comparing sedentary and moderate/vigorous activity before and after participation. We hypothesise that sedentary and moderate/vigorous activity will be improved after the program and this will be maintained at 3, 6 and 12 months post intervention.

2) comparing physical status before and after participation. We hypothesise that adiposity, cardiovascular fitness, muscle strength and power and coordination will be improved after the program and this will be maintained at 3, 6 and 12 months post intervention.

3) comparing food intake before and after participation. We hypothesise that intake of fruits and vegetables will be increased and intake of “extra” foods will be reduced after the program and this will be maintained at 3, 6 and 12 months post intervention.

4) comparing mental health status before and after participation. We hypothesise that mental health will be improved after the program and this will be maintained at 3, 6 and 12 months post intervention.

5) comparing perceived quality of life before and after participation. We hypothesise that quality of life will be improved after the program and this will be maintained at 3, 6 and 12 months post intervention.

We will also explore the influence of adolescent gender, baseline status, readiness to change, self efficacy, emotional eating and parental status and family function on changes in adolescent outcomes. Process evaluation will also be conducted to assess program fidelity, satisfaction and adverse outcomes.

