**Summary**

Given the large proportion of Australian adolescents currently overweight it is clear current practices are insufficient. In order to avoid the expected trajectory to morbid obesity [25] Australian [26] and international [27] researchers have recommended urgent evaluation of interventions targeting overweight adolescents.

The recent evidence of the lack of efficacy of a GP delivered intervention for children [28] and promising early results from two multi-disciplinary community-based overweight adolescent programs [29-30] aligns with earlier expert panel recommendations for “comprehensive multi-disciplinary intervention…[to] encourage healthy behaviours while using techniques to motivate patients and families..” [14] (p.254). The most recent systematic reviews [11-12] have confirmed this approach. Oude et al [11] identified critical issues for future research including: interventions for different levels of severity (we will target overweight and mildly obese), strategies for long-term maintenance (we will work with communities and families to identify sustainability factors), family characteristics which promote success (our process assessment with collect this), adolescent psychosocial factors which influence change (our broad evaluation framework will capture this), resource-effective methods for delivering interventions in different settings (we will evaluate this in metropolitan and regional community settings), and potential harm and benefits of intervention (we will monitor adverse effects as well as health outcomes).

Given the current evidence and strong recommendations for urgent action on this ‘global epidemic’ [11] this project will build on published evidence, recent pilot work and team experience to refine and implement a multi-disciplinary family-centred community-based intervention intended to influence the physical activity, nutrition and psychosocial behaviours of overweight adolescents

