**Methods**

**Intervention:** The intervention will be based on a successful pilot program conducted by the research team that in turn was based on current evidence for the management of adolescent obesity [11, 30-31] and the successful “Fitmatters” program conducted in a tertiary clinical setting. Key strategies of the intervention were: focus on healthy behaviours rather than weight management, multi-disciplinary facilitators and family involvement. The intervention also focussed on the psychosocial aspects of being overweight and was based on to the families’ readiness to change using the PRECEDE-PROCEED Framework [32-35]

The program consists of an 8 week multi-disciplinary family-centred intervention focussed on improving activity, food and attitude habits. Groups of up to 12-15 adolescents and their parents attended 2 hour sessions twice weekly. On each occasion adolescents participated in a 45 minute exercise class involving aerobic, strength and coordination stations. Adolescents also participated in education sessions covering moderate physical activity, sedentary behaviours and diet. Tailored feedback on fitness, screen time and diet were provided to each adolescent. Other sessions provided support and group counselling on setting goals, overcoming set-backs and dealing with cognitive and emotional issues. Adolescents were set ‘homework’ relevant to the stage in the program – for example keeping a diary of TV programs watched. Parents participated in education sessions covering the same issues as the adolescents, sometimes with their child and sometimes separately. Parents also gained informal support from other parents and staff in ‘walk and talk’ sessions, which itself modelled a way of building more activity into their day. Parents were also given practical training in buying and preparing healthy food during a supermarket visit and cooking classes. All sessions were run during school term but out of school hours. A brief program outline is shown in Table 1 (each week has two rows – one for each program day). We intend to include regular contact (SMS, phone, mail) to assist motivation and maintenance of effects after the 8 weeks.

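### Injuries and other physical events from the exercise classes and fitness tests are not among the adverse effects to be monitored, although the protocol's general commitment on harms is unrestricted

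*Protocol*

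**What the plan says.** Two places make a general commitment on harms. The Aims section says: "Process evaluation will also be conducted to assess program fidelity, satisfaction and adverse outcomes". The Background summary takes up potential harm as a research need and answers: "we will monitor adverse effects as well as health outcomes". Neither restricts the kind of harm.

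The Evaluation section, under Process evaluation, turns this into an instruction: "Monitoring will also be conducted for potential adverse effects, specifically: changes in linear height, disordered eating, and psychological well being". It cites the systematic review of obesity interventions that the process evaluation follows. No other section says which adverse effects are monitored.

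On exposure, Methods (Intervention) describes an 8-week program and states: "Groups of up to 12-15 adolescents and their parents attended 2 hour sessions twice weekly". It continues: "On each occasion adolescents participated in a 45 minute exercise class involving aerobic, strength and coordination stations". The Fitness section adds a shuttle test that runs until the participant can no longer keep pace, strength tests in which resistance is raised until the held position gives way, and vertical jumps for maximum height.

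On physical risk, the recruitment section excludes adolescents who "are assessed as unsafe to participate" and requires approval by a medical practitioner. The Background names orthopaedic problems and physical discomfort among the short-term difficulties of obesity.

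**The concern.** The word that introduces the monitoring list makes it a closed list of three items: growth in height, disturbed eating and psychological state. None of them captures a sprain, a fall, an overuse complaint or a faint in a class or test. Exercise is part of every program session, so the list omits the most direct physical risk of a main active component, in a population whose physical vulnerability the protocol itself acknowledges.

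The question is which data are collected. If events are not recorded when they happen, no later analysis plan can recover them. The section on significance expects a stand-alone program that community-based staff could deliver across the country. People deciding on such use would want to know about physical events, and under the stated monitoring the trial could speak only to the three listed harms.

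**Working it through.** There is no stated figure to reproduce. The check sets the text side by side and sizes the exposure.

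**1. Commitment against instruction.** The Aims and the Background summary cover adverse outcomes and effects without limit. Process evaluation names three. Height is a physical measure, but it concerns growth, not injury.

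**2. Where a physical event could enter the data as the protocol stands.**

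| Event | Stated route | Recorded as an adverse effect? |
| --- | --- | --- |
| Injury leading to a missed session | Survey on reasons for non-attendance | No; collected as a barrier to participation |
| Injury leading to withdrawal | Reasons for drop-out | No; collected as a barrier to participation |
| Injury in class, no absence | None stated; session observation, program notes and focus groups might mention it, but are assigned to fidelity and satisfaction | No |
| Injury in a fitness test, no absence | None stated | No |

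The exclusion of those judged unsafe and the medical approval act before entry. They may prevent harm, but they do not count it.

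**3. Scheduled exposure (Methods, Intervention).**

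- Classes per adolescent: 8 weeks × 2 sessions = 16.
- Class time per adolescent: 16 × 45 min = 720 min = 12 hours at full attendance.
- Whole study at the planned recruitment of 124: 124 × 12 = 1,488 class-hours at most. For the 96 required at post-test: 96 × 12 = 1,152.
- Both totals assume that every class is attended. Real exposure would be lower, since the sample-size paragraph itself allows for 30% attrition.

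**4. Testing.** Study design schedules six assessments: initial, pre-program, post-program, and 3, 6 and 12 months after. Each full fitness battery has one shuttle test, three muscle groups tested three times (9 strength trials) and three jumps. Two of the six assessments fall before any class, at the start and end of the wait-list period.

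**5. What recording would make possible.** With no event among n adolescents, the one-sided 95% upper bound on the per-adolescent risk is 1 − 0.05^(1/n).

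- n = 124: 1 − 0.05^(1/124) = 0.024, or 2.4%.
- n = 96: 1 − 0.05^(1/96) = 0.031, or 3.1%.

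Even a result of no injuries would therefore be informative. Without systematic recording, no such bound can be given. The documents contain no injury rate, so an expected number of events would only restate whatever rate was assumed, and none is offered.

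**The case against.** The strongest reply is that this is a choice and not an error. A general commitment is allowed to become specific, and the three items are tied to a cited review. Whether that review supports stopping at three cannot be checked from the protocol. This stands as far as it goes: nothing here is a miscalculation, and the list is defensible for the harms it names. It does not explain why a program with exercise at every session leaves out physical events.

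A second reply is that injuries would not be lost. Absence and drop-out reasons, surveys, focus groups, session observation and program notes are all planned. This stands in part. A reader might infer that injuries are never counted at all, and the protocol does not support that, because an injury that stops attendance has a route into the data. Nor does it say that observations and notes serve fidelity alone; it assigns them to fidelity without barring other use. What remains is that no source is directed at physical events, none classifies them as harms, and events without absence have no stated route.

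Third, a reader might infer that the protocol promises to report harms, or that the trial would declare the program free of adverse effects. It says neither. The verbs are *assess* and *monitor*, and the roll-out statement is not tied to a harms result.

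Finally, entry screening and the gentler start of the modified shuttle test lower the risk, and consent material, which is not in the text at hand, may describe incident handling. The first point lowers the stakes without supplying a count. The second is a reason for caution, not evidence that such text exists.

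**Conclusion.** The point holds in a limited form. The monitoring list is narrower than the protocol's own commitment on harms, and physical events in classes and tests are not monitored as adverse effects. The conclusion rests on reading the three-item list as closed, which is how it is worded, and on finding no other provision in the protocol.

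The size can be stated only as exposure: up to 12 class-hours per adolescent at full attendance, plus physical testing at up to six assessments. It would be tempting to read this as a known number of missed injuries, but the documents give no rate and do not support one.

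The matter is a cheap improvement to harms ascertainment. The primary impact measures, their estimates and the efficacy analysis are not touched.

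**What to change.** Add one item to the list under Process evaluation: *injuries and other physical adverse events during or attributed to exercise classes and fitness tests*.

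Have facilitators note such events on the attendance records already kept for program dose, and have testers note them on the fitness-test records. Start at the initial assessment and continue through the wait-list period, so that events from testing before the program are captured and can be told apart from events in classes. Summarise counts per adolescent and per attended class-hour, taking the denominator from the attendance records.

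The cost is slightly more recording by facilitators and testers. No visit, staff post or outcome measure is added, and the program content does not change. The change has to be in place before the first assessment, because events that go unrecorded cannot be reliably recovered afterwards.
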